## CALCULATION OF THE SIZE OF STUDY

In this trial, the patients were randomized into 2 groups:

- Group 1: group educational intervention by peer educators associated with classical management
- Group 2: classical management without peer education

This is a randomized trial comparing open impact on HbA1c of a 1 year peer education compared to a conventional monitoring alone in health centre.

The comparison group is on HbA1c, the primary judgement criteria. The test is a test of superiority. It is assumed that in the reference group, the value of HbA1c is 8.5% and with a **standard deviation of 2.0**, (previous study conducted in the framework of the NGO Santé Diabète Mali under publication) and we consider that the strategy would be interesting if the assessed value of the mean HbA1c decreased by 1 percentage point of HbA1c and the standard deviation of 0.5 .

In this situation, with a risk  $\alpha$  of 5% and a power  $1-\beta$  of 80%, we must include 60 patients in each group.

in order to take into account a proportion up to 20% of patients lost of sight, we decided to recruit 75 patients per group that is to say 150 patients in total.

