### **Inclusion criteria**

- Patients followed in the diabetes units of the project area and doing regular consultations
- Patients with type 2 diabetes or treated or not with insulin
- Poorly controlled diabetes with HbA1c  $\geq 8\%$
- Patients who accepted to undergo the whole process of peer education
- Patients who agreed to perform all biological measures included in the protocol
- Patients aged from 30 to 70 years old

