### **Main judgment criteria**

The main judgement criteria on which the analysis will be done to comply with the superiority of the contribution of a group educational approach by the peer will be the evolution of the HbA1c from the inclusion to 1 year:

- the HbA1C gives a reliable reflection of the glycemic control that is not subject to short-term variations or bias caused by the social aspects that may influence self-evaluation of data;
- it responds directly to all practices that peer education aims to change (diet and exercise, self glucose monitoring, proper use of drugs etc ...)
- It is the most important physiological parameter to improve for people with diabetes, as it is related to the probability of occurrence of micro-and macro vascular complications.

For the measurement of glycated hemoglobin, the apparatus used will be the machine "Infopia". The preservation of the reagent throughout the study will be precisely monitored to avoid, with high temperatures, deterioration of reagents and therefore invalid action. The reagents will be stored in reagents storage structures of the laboratories of the health facilities involved. The measures will be undertaken by the laboratory assistants of the structures involved in the project and who will have been beforehand trained.

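### The 60 patients per group do not follow from the stated planning inputs, and the 80% power matches no reading of the two printed standard deviations

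*Supplement*

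**What the plan says.** The protocol's section on the size of the study describes a two-group comparison of HbA1c and states that "The test is a test of superiority". It does not say whether the test is one- or two-sided, and it gives no formula.

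The inputs are:

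- Reference group: the section assumes that "in the reference group, the value of HbA1c is 8.5% and with a" standard deviation of 2.0, taken from a previous study not yet published.
- Effect of interest: the mean HbA1c "decreased by 1 percentage point of HbA1c and the standard deviation of 0.5".
- Error rates: alpha "of 5% and a power" of 80%.

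The conclusion is that "we must include 60 patients in each group", raised to 75 per group (150 in total) to allow for up to 20% lost to follow-up.

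The history of protocol updates records that version 2.0 was issued to correct the SD in this paragraph to 2.0. The current text carries both the 2.0 and the 0.5.

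Under the main judgment criteria, the primary outcome is "the evolution of the HbA1c from the inclusion to 1 year". The statistical methods section plans a between-group analysis of variance at p < 0.05.

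**The concern.** A sample size statement should be reproducible from the inputs printed beside it. Here there are two SDs, and nothing says what the second one denotes: the SD in the intervention group, a reduction in the SD, the SD of the change, or the standardised effect (1/2.0 = 0.5). These meanings lead to different sample sizes.

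The inputs also describe a level of HbA1c, while the primary criterion is a change from inclusion. For a change, the relevant SD depends on the correlation between baseline and 12 months, and neither that SD nor that correlation is given.

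The 80% is the only power justification in the protocol. If it does not follow from the inputs, a reader cannot tell what difference the trial was designed to detect, and a non-significant result is harder to interpret.

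**Working it through.** **Inputs.** From the sample size section: difference d = 1 point, reference SD 2.0, second figure 0.5, alpha 5%, power 80%, 60 per group, 20% loss. Allocation is 1:1 (two groups of 75). Two-sided testing is an assumption, because sidedness is not stated.

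**The step that reproduces.** 60/(1 − 0.20) = 75 per group, 150 in total. The allowance for losses is correct.

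**The step that does not.** The normal-approximation formula for two means is

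n per group = (z₀.₉₇₅ + z₀.₈₀)² × (s₁² + s₂²)/d², with (1.96 + 0.8416)² = 7.849.

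| Reading of the SDs | Calculation | n per group, normal | n per group, t or Welch t | Power at 60, t or Welch t | Power at 60, normal |
|---|---|---|---|---|---|
| 2.0 and 0.5 | 7.849 × (4 + 0.25) = 33.4 | 34 | 36 | 95.9% | 96.4% |
| 2.0 falling by 0.5 to 1.5 | 7.849 × (4 + 2.25) = 49.1 | 50 | 51 | 86.7% | 87.3% |
| 2.0 in both groups | 7.849 × (4 + 4) = 62.8 | 63 | 64 | 77.5% | 78.2% |

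Reading 0.5 as the standardised effect 1/2.0 is the same as the third row.

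**One-sided 5%.** The multiplier becomes (1.645 + 0.8416)² = 6.183. The three readings give 26.3, 38.6 and 49.5, so 27, 39 and 50. None is 60.

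**What would give 60.** Solving 60 = 7.849 × 2s² gives a common SD of about 1.955. With a reference SD of 2.0, the second SD would have to be about 1.91. Neither value is in the protocol.

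**Size of the gap under a common SD of 2.0.** The gap is 3 to 4 patients per group. Power by t-test is 77.5% with 60 evaluable per group, 80.1% with 64 (a loss of about 15% from 75) and 86% if all 75 are evaluable.

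**Analysis of the change.** If the SD is 2.0 at each visit and the baseline-to-12-month correlation is r, the SD of the change is 2.0 × √(2(1 − r)). The protocol gives no r, so the following values are assumed.

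| Assumed r | 0.3 | 0.4 | 0.5 | 0.6 |
|---|---|---|---|---|
| Power at 60 per group, unadjusted change (t-test) | 63% | 70% | 77.5% | 86% |

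Setting 7.849 × 2 × 4 × 2(1 − r) = 60 gives r of about 0.52. With a baseline-adjusted ANCOVA the residual SD is about 2.0 × √(1 − r²): 1.91 at r = 0.3 and 1.73 at r = 0.5. Power at 60 per group is then about 81% and 88%.

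**The case against.** The strongest reply is that 60 may be adequate, or even have a sound basis that was left out. Four parts of it deserve an answer.

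- **Other readings favour the trial.** In this translated sentence the verb may govern both nouns, so that the SD falls by 0.5 to 1.5. Power at 60 is then about 87%, and with SDs of 2.0 and 0.5 it is about 96%. This stands. A reader might infer that a common SD of 2.0 is the only credible reading and that the trial is therefore underpowered; the documents do not establish that.
- **A change-score calculation could give 60.** A correlation near 0.52 would do so. The protocol states no such correlation, so this cannot be confirmed, but it rules out saying that no conceivable calculation yields 60. What can be said is that the printed inputs do not.
- **The shortfall is small and 60 is the worst case.** This also stands. Recruiting 75 allows for up to 20% loss; at about 15% loss a common SD of 2.0 already gives 80.1%.
- **The text does not say that 0.5 is the intervention-arm SD.** A reader might argue that the figure is implausible because it implies a 94% fall in variance (0.25 against 4.0). That presupposes one meaning of the 0.5, so it cannot carry the point.

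A reader might also set the reference mean of 8.5% against the entry criterion of at least 8%. The mean does not enter the formula, and 8.5% could be a 12-month value, so nothing about the sample size follows from it.

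None of this removes the central fact: the stated 60 at 80% is not reproduced by any of the readings of the two SDs examined here.

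**Conclusion.** The sample size statement is wrong as written. From the printed inputs, the requirement is 34 to 36, 50 to 51 or 63 to 64 per group, depending on what the 0.5 means. Power at 60 evaluable is about 96%, 87% or 77.5% (78.2% by normal approximation). The 80% corresponds to none of these.

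The conclusion rests on a two-sided 5% test and a 1-point difference; one-sided testing does not rescue the figure. The change-score and ANCOVA powers rest on assumed correlations. They show only that a calculation for the stated primary criterion cannot be checked from the protocol.

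Severity is moderate. A planning figure needs restating, but the documents do not show that the trial is too small.

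**What to change.** In the section on the size of the study:

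1. State what the 0.5 denotes, or remove it.
2. State the SD used, whether the test is one- or two-sided, and the formula.
3. Restate the figure that the design delivers. With a common SD of 2.0 and a two-sided 5% test, that is about 78% power for a 1-point difference at 60 evaluable per group, and 86% if all 75 are evaluable.
4. Say whether the calculation refers to the level of HbA1c or to its change from inclusion. If it refers to the change, give the SD of the change or the baseline correlation.

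Optionally, base the calculation on a baseline-adjusted ANCOVA with the correlation stated as an assumption. With 60 per group this gives about 81% at r = 0.3 and 88% at r = 0.5. The statistical methods section would then have to name ANCOVA as the primary analysis.

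The cost is protocol wording, plus a change to the named primary analysis if the ANCOVA option is taken. Recruitment stays at 75 per group and no extra patients are needed.

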### **SECONDARY JUDGMENT CRITERIA**

The secondary judgement criteria will be of 2 types:

- Clinical and biological criteria:

- ☐ intermediate evolution of the HbA1c, between 0, 3 months, 6 months and 12 months
- ☐ evolution at T = 0, 3 months, 6 months and 12 months of the systolic and diastolic blood pressure, weight, BMI and waist measurement.

To measure the blood pressure, armbands of different sizes (normal and obese) are available. The adequate armband will be placed on the upper arm and inflated with a manometer, to measure blood pressure using a stethoscope placed in the hollow of the arm on the artery. The systolic and diastolic pressure will be measured. The blood pressure will be measured on the right arm after a rest period of 5 min. The average of the two measurements taken at two minute intervals will be used.

To measure the weight, the scale 'seca' will be placed on a wooden board. As it is not possible to ask the patient to undress, we will estimate the weight of his/her clothes and it will be subtracted from the recorded measurement on the survey form.

To measure the size, a portable measuring apparatus will be installed on a flat surface. Patients must remove their shoes and their chech (headscarf). The legs will be joined and heels placed against the back wall of the apparatus. The patient should stand up straight and look ahead.

All equipment used will be new and in duplicate. This will enable us to ensure a quality control of the measures conformity, comparing the results between the two copies of the same equipment.

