## STATISTICAL METHODS USED

The data will be analyzed by a medical epidemiologist with the Epi Info software.

Initially, we will proceed to the description of the included patients and compare the characteristics of both groups of patients to detect any differences at inclusion. These characteristics are expressed as percentage for qualitative variables and as mean and median and their dispersions parameters, respectively, standard deviation and interquartile 25 and 75. The comparison of characteristics between the two groups will be performed using appropriate tests, the exact X2 or Student's t-test. Then, a uni-variable analysis of variance analysis type will be conducted to identify variables to include in the multivariable explanatory models. The inclusion threshold chosen will be 0.25. Data will be expressed as means  $\pm$  SD unless indicated otherwise. Comparisons within groups were performed using analysis of variance by comparing the averages using the comparison test of averages or the Student's t-test.

The comparison between groups will be conducted by analysis of variance, using the Bonferroni correction where appropriate. The results will be statistically significant at  $p < 0.05$ .

**Direct beneficiaries in Mali:** The 150 diabetic patients directly reached by the activities / The 15 peer educators trained in the action areas selected in Mali. The 25 health agents of the action areas selected in Mali / Families and relatives of patients reached by animations (10 000 persons)

**Indirect beneficiaries in Mali :** All the diabetic patients of Mali (3% of the adult population) / All the health workers involved in the management of diabetes in Mali / The Malian health systems / The Malian population by reducing the risk factors of diabetes and increasing the quality of life

**Indirect beneficiaries in Africa:** Diabetic patients of French and English speaking African countries which will benefit from the methodology and tools developed

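### The plan allows for up to 20% loss but has no missing-data rule, so the primary ANOVA of HbA1c change drops patients without a 12-month value and makes no use of their 3- and 6-month values

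*Supplement*

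**What the plan says.** - **Expected loss.** Under *Calculation of the size of study* the protocol first requires 60 patients per group, then adds: "in order to take into account a proportion up to 20% of patients lost of sight, we decided to recruit 75 patients per group". This inflation is its only provision for loss to follow-up.
- **Primary criterion.** *Main judgment criteria* names the "evolution of the HbA1c from the inclusion to 1 year".
- **Method.** *Statistical methods used* says: "The comparison between groups will be conducted by analysis of variance, using the Bonferroni correction where appropriate". The software is Epi Info. The section also mentions multivariable explanatory models, with covariates screened at 0.25, but gives neither their form nor their outcome. It defines no analysis population, intention-to-treat rule, missing-data method or sensitivity analysis.
- **Interim HbA1c.** *Secondary judgment criteria* lists the "intermediate evolution of the HbA1c, between 0, 3 months, 6 months and 12 months", and the secondary objectives include a between-arm comparison at 3, 6 and 12 months. The chronogram shows laboratory tests at T0, T3, T6 and T12.

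**The concern.** An analysis of variance on the 0-to-12-month change needs both values. With no imputation rule, a patient seen at 0, 3 and 6 months but not at 12 contributes nothing to the primary result, although the trial already holds three HbA1c values for that patient.

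The trial is open and only one arm is asked to attend group sessions, so loss could differ between arms and could be related to how control is developing. If so, the patients who remain are no longer comparable by randomisation, and a larger sample gives the same biased answer with a narrower interval. The interim values are the information best placed to correct this, and the primary comparison does not use them.

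**Working it through.** **1. The plan's own figure.** 60 / (1 − 0.20) = 75 per group and 2 × 75 = 150, as stated. At the 20% ceiling, 75 − 60 = 15 patients per arm, or 30 of 150, have no primary outcome.

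**2. Inputs.** From the protocol: SD 2.0, target difference 1.0 point, 75 per arm, up to 20% loss, HbA1c at 0, 3, 6 and 12 months. Not in the protocol, so assumed: within-patient correlations and the pattern of loss.

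**3. Size of bias, loss related to observed values in the education arm only.** Simulation with 400,000 patients per arm, no true effect, correlations between visits of 0.5 to 0.7, 20% loss per arm, random in controls. The log-odds of loss rise by 0.5, 1.0 or 1.5 per SD (odds ratio 1.6 to 4.5). Entries are spurious benefit in HbA1c points.

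| Loss follows | Change among patients with T12 | Using 0-, 3- and 6-month values |
|---|---|---|
| 6-month level | 0.03 / 0.05 / 0.07 | about 0.01 or less |
| 0-to-6-month change | 0.14 / 0.24 / 0.31 | about 0.01 or less |

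A second set of correlations in the same range gave 0.011 / 0.034 / 0.051 for the first row's change analysis. The range for level-driven loss is therefore about 0.01 to 0.07.

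**4. Trial-sized check.** 75 per arm, 4,000 replicates, true effect −1.0, correlation 0.3 + 0.7·r^(months/3) with r = 0.5, 0.7, 0.9, log-odds slope 1 per SD, about 16–19% missing at month 12 only. Entries are mean estimates for the three values of r.

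| Loss | ANOVA of change | Mixed model |
|---|---|---|
| Completely random | −1.00, −1.00, −1.00 | −1.01, −1.00, −1.00 |
| Education arm, 6-month level | −1.01, −1.00, −1.00 | −1.01, −1.00, −1.00 |
| Education arm, early change | −1.20, −1.15, −1.06 | −1.01, −1.00, −1.00 |
| Both arms, same direction, early change | −0.93, −0.95, −0.97 | −0.99, −1.00, −0.99 |
| Arms in opposite directions, early change | −1.43, −1.35, −1.15 | −1.00, −1.00, −1.00 |
| Arms in opposite directions, unobserved 12-month level | −1.42, −1.34, −1.15 | −1.50, −1.38, −1.17 |

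The bias can go either way, is near nil in some patterns, and is not repaired by the mixed model in the last row.

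**5. Precision.** With 60 per arm and correlation ρ between 0 and 12 months:
- Unadjusted change: SE = 2.0 × √[2(1 − ρ)] × √(2/60). For ρ = 0.5: 2.0 × 1 × 0.183 = 0.37. For ρ = 0.7: 2.0 × 0.775 × 0.183 = 0.28.
- Baseline-adjusted: SE = 2.0 × √(1 − ρ²) × √(2/60). For ρ = 0.5: 2.0 × 0.866 × 0.183 = 0.32. For ρ = 0.7: 2.0 × 0.714 × 0.183 = 0.26.

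Under completely random loss in step 4, the empirical SE was 0.41, 0.37, 0.25 for change and 0.33, 0.31, 0.23 for the mixed model.

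**6. Bias against noise.** With SE 0.37, a bias of 0.07 is 0.07/0.37 = 0.19 SE; 0.14 is 0.38 SE; 0.31 is 0.84 SE.

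**The case against.** Several parts of the case against this point stand.

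- **The protocol nowhere says that only completers are analysed.** That is the consequence of ANOVA on change with no imputation rule, not a stated choice. Nor does sizing on 60 mean that 60 are expected: 20% is a ceiling.
- **A reader might infer that the interim HbA1c is ignored.** It is not; it is a secondary objective and criterion. It is only absent from the primary comparison.
- **A reader might infer that patients who miss sessions will be removed from the education arm**, from the criterion "Patients who accepted to undergo the whole process of peer education". That is a condition at entry, checked when patients are selected. Nothing provides for later removal, and missing a session is not the same as missing the 12-month measurement.
- **A reader might infer that the mixed model is less biased whatever the loss.** It is so only when loss depends on observed values and is related to outcome. For loss that follows the 6-month level, the planned change analysis is itself nearly unbiased. For loss driven by the unseen 12-month value, neither method is sound.
- **No separate analysis plan is shown**, and analysis sets and missing-data rules often sit there. This does not dispose of the point: the protocol itself names the between-group method, and the proposal replaces that method with a better one using data already scheduled.

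**Conclusion.** The point holds in a limited form and should be acted on. For a trial that allows for up to 20% loss, the stated primary comparison discards patients without a 12-month value and leaves their earlier follow-up HbA1c unused. Inflation to 75 per arm does not address the resulting bias.

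How large that bias would be is not known. Under the assumed patterns of step 3 it is small for level-driven loss and reaches roughly a third of the 1.0-point target at the upper end for loss that follows early change. With more stable HbA1c (r = 0.9 in step 4) one-arm loss on early change gives only about 0.06. These figures rest on assumed correlations and loss mechanisms, because the protocol gives neither. The documents do not show that loss will be informative, or in which direction. The gain in precision does not depend on informative loss: at ρ = 0.5 baseline adjustment alone cuts the standard error from about 0.37 to 0.32.

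**What to change.** State in *Statistical methods used*:

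- **Analysis set.** All randomised patients in their assigned arm, regardless of sessions attended.
- **Primary model.** One mixed model for repeated measures on HbA1c at 3, 6 and 12 months, with group, visit, group-by-visit, baseline HbA1c and baseline-by-visit, and unstructured covariance. The 12-month group contrast is primary; the 3- and 6-month contrasts serve the secondary objective.
- **Sensitivity analysis.** A delta-shift analysis for loss not at random: worsen the values implied for missing 12-month patients by a range of amounts and report where the conclusion changes. For scale, with 20% missing in one arm, a shift of 1.0 point in that arm moves the estimate by 0.20 × 1.0 = 0.20.

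**Cost.** Mixed-model software in place of Epi Info and a little more analysis work; no extra patients or scheduled visits. Tracing patients who stopped attending to obtain their 12-month HbA1c would help against the loss that no model repairs, but it is additional field work and should be budgeted as such.

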## STATISTICAL METHODS USED

The data will be analyzed by a medical epidemiologist with the Epi Info software.

Initially, we will proceed to the description of the included patients and compare the characteristics of both groups of patients to detect any differences at inclusion. These characteristics are expressed as percentage for qualitative variables and as mean and median and their dispersions parameters, respectively, standard deviation and interquartile 25 and 75. The comparison of characteristics between the two groups will be performed using appropriate tests, the exact X2 or Student's t-test. Then, a uni-variable analysis of variance analysis type will be conducted to identify variables to include in the multivariable explanatory models. The inclusion threshold chosen will be 0.25. Data will be expressed as means  $\pm$  SD unless indicated otherwise. Comparisons within groups were performed using analysis of variance by comparing the averages using the comparison test of averages or the Student's t-test.

The comparison between groups will be conducted by analysis of variance, using the Bonferroni correction where appropriate. The results will be statistically significant at  $p < 0.05$ .

**Direct beneficiaries in Mali:** The 150 diabetic patients directly reached by the activities / The 15 peer educators trained in the action areas selected in Mali. The 25 health agents of the action areas selected in Mali / Families and relatives of patients reached by animations (10 000 persons)

**Indirect beneficiaries in Mali :** All the diabetic patients of Mali (3% of the adult population) / All the health workers involved in the management of diabetes in Mali / The Malian health systems / The Malian population by reducing the risk factors of diabetes and increasing the quality of life

**Indirect beneficiaries in Africa:** Diabetic patients of French and English speaking African countries which will benefit from the methodology and tools developed

**Sustainability plan:** The project implements an inclusive approach in existing systems. Ability building will be targeting diabetic people of the country and professionals of the public service included in the health pyramid. The institutionalization of the project will be done through the capitalization of the action in the national programs of prevention and fight against diabetes and in national research programs. Strengthening will be provided to local partners through training of its members to project management and raise funds so that the partner can invest in the sustainability of the action. A protocol for monitoring and evaluation was prepared for the results of that action can be validated and published. The expertise at the regional level will enable the IDF Africa to develop a sub regional strategy, this project represents an opportunity to bring new financial and technical partners on this issue.

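### No single primary model is fixed for change in HbA1c; a pre-specified ANCOVA on baseline HbA1c would be more precise than the stated analysis of variance

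*Supplement*

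**What the plan says.** Under *Main judgment criteria*, the protocol (version 2.0) sets the primary criterion as "the evolution of the HbA1c from the inclusion to 1 year". Under *CALCULATION OF THE SIZE OF STUDY* it states "The test is a test of superiority", takes a "standard deviation of 2.0" in the reference group and a 1-point effect, and arrives at 60 evaluable patients per group (75 recruited).

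Three steps under *STATISTICAL METHODS USED* bear on the treatment comparison:

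- A description of the sample, including tests to "compare the characteristics of both groups of patients to detect any differences at inclusion".
- A separate model-building step: "a uni-variable analysis of variance analysis type will be conducted to identify variables to include in the multivariable explanatory models". The rule is "The inclusion threshold chosen will be 0.25".
- The group comparison: "The comparison between groups will be conducted by analysis of variance, using the Bonferroni correction where appropriate".

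The section lists no candidate variables for the screen and no covariate for the group comparison. Adjustment for baseline HbA1c is mentioned nowhere in the protocol. Nor does the section say whether the analysis of variance or a multivariable model supplies the primary estimate. It also provides for tests within groups, without saying what role they play in judging efficacy.

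Baseline HbA1c will be available. Entry requires HbA1c of at least 8% (*Inclusion criteria*), the secondary criteria list HbA1c at 0, 3, 6 and 12 months, and the *Chronogram* schedules laboratory tests at T0.

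**The concern.** Two things are left on the table.

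The first is precision. Change in HbA1c is correlated with its own baseline. A comparison of change that ignores baseline carries variance that a single covariate would remove. The planned size has no margin: with SD 2.0 for the 12-month value and 60 per arm, power is already slightly below the stated 80%.

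The second is that the plan allows at least two treatment estimates, one crude and one from a model whose content depends on the data, with no order of precedence. The trial is open-label, so it matters that the model is settled before results are seen. If the more favourable of the two were reported, the 5% error rate would not hold.

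**Working it through.** **Inputs from the protocol.** SD 2.0, effect 1.0 point, α 5%, power 80%, 60 evaluable per group. Sidedness is not stated; two-sided is assumed. SD 2.0 is applied to both arms. (The sample-size paragraph also mentions an SD of 0.5, which is a separate matter.)

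**Input not in the protocol.** The correlation r between baseline and 12-month HbA1c. A range of 0.3, 0.5 and 0.7 is assumed.

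**The plan's own figure.** n = 2 × 2.0² × (1.960 + 0.842)² / 1² = 62.8, so 63 per group (64 by the t distribution), against 60 stated. With SDs of 2.0 and 0.5, n = (4 + 0.25) × 7.849 = 33.4, so 34. Neither gives exactly 60. Power at 60 per group with SD 2.0 is 78.2% (normal) or 77.5% (t). The inflation 60 / 0.80 = 75 reproduces.

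**Step 1: equal SD of 2.0 at both times.**

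- SD of change = 2.0 × √(2(1 − r))
- Residual SD of ANCOVA = 2.0 × √(1 − r²)
- Variance ratio, ANCOVA to change = (1 + r)/2

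Power by the t distribution, 60 per arm:

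| r | SD change | SD ANCOVA | Variance ratio | Power, change | Power, ANCOVA | Gain (points) |
|---|---|---|---|---|---|---|
| 0.3 | 2.37 | 1.91 | 0.65 | 63.1% | 81.3% | 18 |
| 0.5 | 2.00 | 1.73 | 0.75 | 77.5% | 88.0% | 10 |
| 0.7 | 1.55 | 1.43 | 0.85 | 93.9% | 96.7% | 3 |

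**Step 2: allow for the entry rule.** Requiring HbA1c of at least 8% narrows the baseline distribution. Assume a normal source population with mean 8.5 and SD 2.0, cut at 8. The cut lies at (8 − 8.5)/2 = −0.25, and the normal density over the upper tail there is 0.646. Baseline variance becomes 4 × (1 − 0.646 × (0.646 + 0.25)) = 1.69, an SD of about 1.30. Selection on baseline leaves the regression slope r and the residual variance 4(1 − r²) unchanged, where r is now the source-population correlation. So Var(change) = 4(1 − r²) + (1 − r)² × 1.69:

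| r (source) | Var(change) | Variance ratio | Power, change | Power, ANCOVA | Gain (points) |
|---|---|---|---|---|---|
| 0.3 | 3.64 + 0.83 = 4.47 | 0.82 | 73% | 81% | 8 |
| 0.5 | 3.00 + 0.42 = 3.42 | 0.88 | 84% | 88% | 4 |
| 0.7 | 2.04 + 0.15 = 2.19 | 0.93 | 96% | 97% | 1 |

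**Step 3: when does ANCOVA reach 80%?** At r = 0.20 the residual SD is 1.96 and power is 79.2%. At r = 0.25 it is 1.94 and power is 80.1%. So r must be about 0.25 or more.

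**Step 4: the screened model.** Simulation with equal SDs, 60 per arm, 4,000 runs per setting, change as outcome, and baseline HbA1c plus ten pure-noise variables offered to a p < 0.25 screen:

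| r | Type I error: change / screened / ANCOVA | Smaller p of change and screened | Power: change / screened / ANCOVA |
|---|---|---|---|
| 0.3 | 4.4 / 4.7 / 4.8% | 7.2% | 64.0 / 80.2 / 81.6% |
| 0.5 | 5.3 / 4.8 / 4.8% | 7.7% | 77.7 / 85.3 / 87.1% |
| 0.7 | 5.1 / 4.9 / 5.2% | 7.1% | 93.6 / 95.5 / 96.4% |

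The screen picked baseline HbA1c in at least 99.7% of runs.

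**The case against.** The best defence has four parts.

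*The plan does not say the comparison is unadjusted.* That is inferred from the absence of a named covariate, and multivariable models are planned. This stands as a caution. It does not rescue the plan, because nothing says those models supply the primary result or that baseline HbA1c is a candidate for them.

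*The loss may be small.* This stands in part. The equal-SD figures are the upper end, and the entry rule brings the gain down to about 8, 4 and 1 points. If the screened model were the primary one and baseline HbA1c were offered to it, the loss against ANCOVA would be only about 1 to 2 points.

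*Screening does no demonstrated harm.* A reader might infer that the 0.25 screen inflates the false-positive rate. In the simulation the screened model taken alone held about 5%. Only taking the smaller of two p-values raised it, to 7.1–7.7%, and the plan does not propose that. The weakness is the missing order of precedence. A reader might also infer that the tests for differences at inclusion choose the covariates. The protocol does not say so: the univariable screen is a separate step.

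*The change comparison is unbiased.* This stands. A chance baseline imbalance shifts the unadjusted result in the sample at hand through regression to the mean, but over randomisations the comparison is unbiased with the correct error rate. The issue is efficiency and pre-specification, not validity.

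**Conclusion.** The point holds in this form: the plan names no single primary model, and the comparison it does state is less precise than an ANCOVA on data it already collects. At 60 per arm the gain in power is about 1 to 18 points for r between 0.3 and 0.7. Where it falls in that range depends on r, which the documents do not give, and on how far the entry rule narrows the baseline spread. It rests on SD 2.0 in both arms and a two-sided 5% test, and it is smaller still if the screened model would have been primary and had included baseline HbA1c.

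It would be tempting to conclude that ANCOVA cures the slight shortfall in the sample size at no cost in patients. The documents do not support that without a value for r: below about 0.25, power at 60 per arm stays just under 80%. This is a change that should be made, but the trial's validity does not hang on it.

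**What to change.** In *STATISTICAL METHODS USED*:

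- Name one primary analysis: a linear model of 12-month HbA1c (or change) on randomised group and T0 HbA1c, two-sided at 5%, reporting the adjusted difference with its 95% confidence interval.
- List any further covariates in advance.
- Keep the models built with the 0.25 screen as secondary and exploratory, and state that they do not supply the primary treatment effect.
- State that efficacy is judged on the between-group estimate, and that within-group tests are not used for that purpose.

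The cost is a few lines of text, settled before the outcome data are examined. No new data, visits or patients are needed.
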